# Introduction

The COVID-19 pandemic and resulting national lockdown has had a profound impact on the delivery of healthcare with the reconfiguration of acute services to support the anticipated influx of COVID-19 patients, cancellation of most elective activity and pausing of screening programmes (1). There is also evidence of a change in healthcare-seeking behaviour, for example, in Scotland the uptake of both emergency and elective hospital based care dropped substantially over the lockdown period (2). However, within child health, key routine services such as childhood immunisations and health visiting continued across Scotland and a campaign launched in April 2020 urged the public to remember “The NHS is open” (https://www.gov.scot/news/urgent-medical-help-still-available).

It has become increasingly apparent that younger children are at low risk of severe disease due to SARS-CoV-2 (3, 4) and may be less susceptible to infection by the virus (5). Yet the wider impact of the pandemic on children in terms of education, mental and physical health and safeguarding is not yet fully understood, though it is likely to be profound (6, 7). One particular area of concern early in the lockdown period was the potential effect on the uptake of routine childhood immunisations (8). Maintaining high population vaccine coverage is vital for both direct and indirect (via herd immunity) protection against non-COVID-19 infectious diseases. The current pre-school UK vaccination schedule is shown in table 1 along with the disease protected against.

Table 1 UK immunisation schedule 2020 (9). NA= not referenced/used in this manuscript.

| Age due | Diseases protected against | Vaccine given | Referred in this manuscript as: |
| --- | --- | --- | --- |
| 8 weeks | Diphtheria, tetanus, pertussis (whooping cough), polio, Haemophilus influenzae type b (Hib) and hepatitis B | DTaP/IPV/Hib/HepB | First dose 6in1 |
|  | Meningococcal group B (MenB) | MenB | NA |
|  | Rotavirus gastroenteritis | Rotavirus | NA |
| 12 weeks | Diphtheria, tetanus, pertussis, polio, Hib and hepatitis B | DTaP/IPV/Hib/HepB | Second dose 6in1 |
|  | Pneumococcal (13 serotypes) | Pneumococcal conjugate vaccine (PCV) | NA |
|  | Rotavirus gastroenteritis | Rotavirus | NA |
| 16 weeks | Diphtheria, tetanus, pertussis, polio, Hib and hepatitis B | DTaP/IPV/Hib/HepB | Third dose 6in1 |
|  | Meningococcal group B (MenB) | MenB | NA |
| 1 year (after first birthday) | Hib and Meningococcal group C (MenC) | Hib/MenC | NA |
|  | Measles, mumps and rubella | MMR | First dose MMR |
|  | Pneumococcal | PCV booster | NA |
|  | MenB | MenB booster | NA |
| 3 years 4 months (or shortly after) | Diphtheria, tetanus, pertussis and polio | dTaP/IPV | NA |
|  | Measles, mumps and rubella | MMR booster | Second dose MMR |

Initial reports suggested a fall in children receiving their scheduled vaccinations in the very early lockdown period (8). The aim of this paper is to use routinely collected and publicly available child health surveillance data in Scotland to describe the pattern of pre-school vaccine uptake during the pandemic period, with comparisons to 2019 data, by geographical area and socio-economic index. Of note, this paper refers to the first national lockdown which began on 23^rd^ March 2020 with restrictions easing gradually from June 2020. The emergence in the UK of a new, highly transmissible, SARS-CoV-2 variant in late 2020 (10) has since prompted further control measures (essentially further lockdowns in Scotland and England with similar measure in Wales and Northern Ireland). Data continue to be collected on the impact on vaccine uptake and should be further evaluated when available, however this paper deals solely with the first national lockdown period.

We have contacted colleagues in child health surveillance from the other nations of the UK (England, Wales and Northern Ireland) to request access to equivalent data and should this become available, we will aim to describe the patterns of pre-school vaccine uptake as above for each of the nations which form the UK.

# Aims and objectives

## Aims

We aim to describe the impact of COVID-19 and associated control measures on the uptake of pre-school immunisations in Scotland, with potential to expand to other UK nations should additional data become available.

## Objectives

We seek to:

1. Describe the impact of the COVID-19 pandemic on the uptake of selected immunisations provided at each of the five immunisation contacts offered to pre-school children (table 1)
2. Explore whether impact varied by: i) Health and social care partnership area of residence (HSCP- geographical areas closely related to local authority areas); and ii) socio-economic deprivation index
3. Use these data to inform future strategies to promote maximal childhood vaccine uptake and reduce barriers, both in the context of a pandemic and more generally.

# Study Design

## Study design

Natural experiment, designed to take advantage of routinely collected data in the year prior to the COVID-19 pandemic and immediately before, during the first period of ‘lockdown’ (23 March-July 2020) imposed by the Scottish and UK and other devolved governments, and after the lockdown restrictions began to be eased (August- September 2020).

## Setting

Scotland, UK with potential scope to extend to England, Wales and Northern Ireland.

## Population

All children in Scotland (and if available; England, Wales and Northern Ireland) who become eligible (based on age), for routine immunisations as shown in Table 1 (specifically; first, second and third dose 6 in1, and first and second dose MMR) from January 2019 to September 2020.

## Data sources

The Public Health Scotland (PHS) [COVID-19 wider impacts dashboard](https://scotland.shinyapps.io/phs-covid-wider-impact/_w_c89e0e10/) (<https://scotland.shinyapps.io/phs-covid-wider-impact/>), which presents data drawn from the Scottish Immunisation & Recall System (SIRS). SIRS is the dataset which records all information on children eligible for and receiving routine preschool immunisation in Scotland. These data are publicly available via the link above.

Equivalent data has been sought from England, Wales and Northern Ireland.

In England, data are extracted from ImmForm, a Public Health England website used to collect vaccine coverage data and provide vaccine ordering facilities. At present, due to data sharing agreements, it is likely that data from England will be analysed “in-house” by scientists at Public Health England, and results shared with the wider team. This analysis plan and the code used to analysis the Scottish data will be shared and similar methods applied within the constraints of which data are available (likely uptake of 6in1 vaccine at 6 months of age, and MMR at 12 and 18 months).

In Northern Ireland, data are collected by the Northern Ireland Child health System, the format and accessibility of which is being explored.

In Wales, data are provided by NHS Wales Informatics Service from the National Community Child Health Database (NCCHD). This is sourced from Community Child Health databases maintained by local Child Health Office staff in Trusts throughout Wales based on regular returns from nurses and doctors who immunise or advise on immunisation.

## Ethical approval

Ethical approval for this specific study was not required as we are using publicly available, anonymised, aggregated data.

## Inclusion/exclusion criteria

All children living in Scotland (or other UK nation) who became eligible based on age for the relevant vaccine are included, with the exception of those registered to receive their second dose MMR immunisation in HSCPs associated with NHS Grampian. This is because this immunisation is offered to children when they turn 4 years of age in Grampian, rather than when they turn 3 years and 4 months of age as in all other Board areas.

Note 1: During this period, some children would become eligible for more than one set of immunisations (for example a child aged 8 weeks in January 2020, would become eligible for first, second and third doses of 6in1 vaccine during the study period). These children are included for each separate dose.

Note 2: A very small number of children would be medically exempt from the MMR vaccine as it is a live vaccine, however these children are still included as eligible for the purposes of this analysis.

Note 3: It is possible for parents to consent to receive selected vaccines only (for example to decline the MMR, but still receive the other vaccines offered at 1 year of age), therefore caution must be taken if extrapolating these data to represent uptake of the other pre-school immunisations for which data are not currently publicly available.

## Sample size calculation

Taking in entire eligible population

# Data and data validation

## Data variables available

Table 2 Available variables (Scottish dataset)

| **Variable** | **Description** | **Values** |
| --- | --- | --- |
| Vaccine type | Type of preschool immunisation vaccine | First dose 6in1 (8 weeks)  Second dose 6in1 (12 weeks)  Third dose 6in1 (16 weeks)  First dose MMR (12 months)  Second dose MMR (3 years and 4 months) |
| Area name | Splits into Scotland as a whole, NHS Health Boards and HSCP | Scotland  NHS Health Boards  HSCP |
| Time-period | Time-period when preschool child was eligible for immunisation | 2019 (baseline),  January to September 2020 (Monthly)  Week beginning 02 March to 28 September 2020 (Weekly) |
| Total eligible | The total number of eligible preschool children | N |
| Total uptake within 4 weeks of eligibility (N)* | The number of preschool children who received vaccination within 4 weeks of becoming eligible | N |
| Total uptake within 4 weeks of eligibility (%) | The number of preschool children who received vaccination within 4 weeks of becoming eligible out of the total number of eligible preschool children | % [0,100] |
| SIMD Quintile (for Scotland level data only) | Scottish Index of Multiple Deprivation (SMID) index | 1 (most deprived), 2, 3, 4, 5 (least deprived) |

*Note: Data are available for total uptake at later ages (for example 6 months of age). However, we have chosen to examine uptake within 4 weeks of eligibility as this represents timely uptake of vaccinations as per the recommended schedule.

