### Exposures of interest

Geographical area, specifically HSCP (excluding partnership areas within NHS Grampian for the MMR second dose only).

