## Missing data

As noted in section 3.6, for analyses relating to the second dose of MMR only, data relating to children registered to receive their immunisations in HSCP within NHS Grampian will be excluded. This is because this immunisation is offered to children when they turn 4 years of age in Grampian, rather than when they turn 3 years and 4 months of age as in all other Board areas.

A small number of children have missing information on HSCP area of residence and/or SIMD quintile. Numbers with missing data will be provided as supporting information for the analyses by HSCP and SIMD. No information is provided through the PHS dashboard on immunisation uptake for children with missing HSCP/SIMD data so this will not be reported.

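### The plan excludes NHS Grampian from all second-dose MMR analyses but does not say how this is done in the SIMD analysis, where counts are listed only for Scotland as a whole

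*SAP*

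**What the plan says.** The eligibility rule (SAP, Inclusion/exclusion criteria) takes in all children eligible by age, "with the exception of those registered to receive their second dose MMR immunisation in HSCPs associated with NHS Grampian". The reason given is that "this immunisation is offered to children when they turn 4 years of age in Grampian", whereas all other Boards use 3 years 4 months.

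The section Missing data repeats the rule for second-dose MMR: "data relating to children registered to receive their immunisations in HSCP within NHS Grampian will be excluded". It makes no exception for any objective.

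The HSCP analysis (objective bi, Exposures of interest) carries the rule forward: "excluding partnership areas within NHS Grampian for the MMR second dose only". The SIMD analysis (objective bii) does not mention Grampian in its Outcome, Exposures of interest or Analytical techniques, yet it promises one table per vaccine, so second-dose MMR is included. It also plans a comparison of each quintile with SIMD 1 within 2019 and within lockdown, to judge whether inequality changed.

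On the data, Table 2 describes the area variable thus: "Splits into Scotland as a whole, NHS Health Boards and HSCP". The deprivation variable is listed as "SIMD Quintile (for Scotland level data only"). Ethical approval states that "we are using publicly available, anonymised, aggregated data".

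**The concern.** An exclusion by area can be applied to aggregate counts only if those counts are split by area. The SIMD counts, as listed, are not. The SAP therefore prescribes a step in objective bii that the listed data do not allow the analysts to carry out, and it does not say that the source has already done so.

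If the SIMD counts include Grampian, the second-dose SIMD results describe a population that the SAP has ruled out, and they cannot be set beside the second-dose results of objectives a and bi. The result most exposed is the comparison of quintiles with SIMD 1. Grampian children need not be spread evenly over the quintiles, so a difference in offer age could be read as a difference by deprivation.

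**Working it through.** The SAP gives no figure to reproduce here. The first step is a check of the text; the second is an illustration on assumed inputs.

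**Step 1. Can the exclusion be applied with the listed variables?**

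| Analysis of second-dose MMR | Split available (Table 2) | Can Grampian be removed? |
| --- | --- | --- |
| Objective a, Scotland | Scotland, Board, HSCP | Yes, by adding up the non-Grampian Boards |
| Objective bi, HSCP | HSCP | Yes, by dropping the Grampian partnerships |
| Objective bii, SIMD | SIMD for Scotland only | No, unless the source has already done so |

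The data are aggregates, so there are no child-level records from which to rebuild the SIMD table.

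**Step 2. What could happen if Grampian is included?**

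Let p be uptake outside Grampian, s the Grampian share of eligible children in a quintile, and g Grampian uptake within 4 weeks as the source counts it. Then

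observed uptake = (1 − s)p + s·g.

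The document gives none of these values; all are assumptions. Below, g = 0, which stands for children counted at 3 years 4 months but not yet offered the dose.

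*Lockdown v 2019 within one quintile, with p = 85% in 2019 and 80% in lockdown, and s the same in both periods.* The true OR is (0.80/0.20)/(0.85/0.15) = 4.00/5.67 = 0.71.

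| s | Observed 2019 | Observed lockdown | Observed OR |
| --- | --- | --- | --- |
| 3% | 82.5% | 77.6% | 0.74 |
| 10% | 76.5% | 72.0% | 0.79 |
| 20% | 68.0% | 64.0% | 0.84 |

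For s = 10%: (0.72/0.28)/(0.765/0.235) = 2.571/3.255 = 0.79. With a constant share and g = 0, the OR moves towards 1. If true uptake does not change between periods, it stays at 1.00.

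*SIMD 5 v SIMD 1 within a period, with p = 50% (SIMD 1) and 60% (SIMD 5) in 2019, and 55% and 70% in lockdown.*

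| Share in SIMD 1, SIMD 5 | OR 2019 | OR lockdown | Lockdown OR / 2019 OR |
| --- | --- | --- | --- |
| 0%, 0% (truth) | 1.50 | 1.91 | 1.27 |
| 10%, 10% | 1.43 | 1.74 | 1.21 |
| 3%, 15% | 1.11 | 1.28 | 1.16 |
| 3%, 20% | 0.98 | 1.11 | 1.14 |
| 15%, 5% | 1.79 | 2.26 | 1.26 |

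For shares of 15% and 5% in 2019, observed uptake is 0.85 × 50% = 42.5% and 0.95 × 60% = 57.0%, so the OR is (0.570/0.430)/(0.425/0.575) = 1.326/0.739 = 1.79.

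At higher uptake (70% and 80% in 2019, 75% and 85% in lockdown), shares of 3% and 20% turn true ORs of 1.71 and 1.89 into 0.84 and 0.80. The gradient can thus be flattened, reversed or steepened. Setting g to 5% changes these results little.

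**The case against.** The strongest reply is that any bias depends on a source that the document does not describe closely enough. The published Scotland-level SIMD figures for this dose may already omit Grampian. Placing the exclusion under Missing data fits that reading, although it is worded as something the analysis will do. If so, no error arises and the SAP lacks only a sentence. This stands as a limit on the consequence. It does not remove the gap, because the population of a planned analysis should be stated and this one cannot be worked out from the SAP.

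A reader might go further and infer that, if Grampian is included, its children are near-certain non-vaccinated entries in the denominator. The document does not support that. Table 2 labels the dose with 3 years 4 months, which points that way, but it defines the time period by when the child was eligible. If eligibility follows the local offer, Grampian children are counted at 4 years with ordinary uptake. The effect would then probably be smaller, though the cohort would be of mixed age and still contrary to the eligibility rule.

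Nor can one infer that odds ratios are always pulled towards 1, or that false differences between quintiles must appear. The pull towards 1 holds for lockdown v 2019 within a quintile under the assumptions shown. It does not hold for the gradient: 1.50 became 1.79 in one case above. With equal shares and equal true uptake, no false difference arises. A gap of about 14 points between quintiles with the same true uptake (82.5% v 68.0% in 2019) needs the extreme pairing of 3% and 20% shares.

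Finally, the scope is narrow: one of five vaccines in an exploratory objective. The primary comparison of 2019 with lockdown for Scotland can be made without Grampian from the Board counts.

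**Conclusion.** The point holds as a conflict between the population rule and the listed data. The SAP excludes Grampian from second-dose MMR analyses without exception and includes second-dose MMR in objective bii, but lists no data from which that exclusion can be made there. It does not say whether the published SIMD counts already reflect it.

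The document does not show that the SIMD results will be biased, and the size and direction of any distortion cannot be found from it. They depend on three unstated facts: whether Grampian is in the SIMD counts, at what age its children are counted, and how they are spread over the quintiles. Under the assumption of counting at 3 years 4 months with no timely uptake, a 10% share moves a within-quintile OR from 0.71 to 0.79. The comparison with SIMD 1 is the more fragile, and its change can go either way.

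This should be settled before the analysis. It does not affect the other four vaccines or the primary comparison.

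**What to change.** Before analysis, for 2019 and for lockdown, add the second-dose MMR eligible counts over the five SIMD quintiles, plus the number with missing SIMD. Compare this with the sum of eligible counts over the non-Grampian Boards, allowing for children with missing area. Alternatively, ask PHS directly.

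Two details matter. The check should use eligible counts, because Missing data says that the dashboard gives no uptake for children with missing HSCP or SIMD. The comparator should be the sum of the non-Grampian Boards; Scotland minus Grampian would subtract Grampian twice if the Scotland figure already omits it.

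If the counts agree, state in objective bii and in Missing data that the SIMD figures exclude Grampian. If Grampian is included, request from PHS the SIMD table without it. If that cannot be supplied, either omit second-dose MMR from objective bii or report it as a declared exception to the exclusion, with the limitation stated. Amend the Outcome, Exposures of interest and Analytical techniques of objective bii, and Missing data, to match.

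The cost is one reconciliation of published totals and at most one tabulation request.

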## Constructed variables

Table 3 Constructed variables

| **Variable** | **Description** | **Values** |
| --- | --- | --- |
| Absolute change from 2019 (%) | % uptake within 4 weeks of eligibility in 2020 – % uptake within 4 weeks of eligibility in 2019 | [-100,100] % |
| Relative change from 2019 (%) | Absolute change from 2019 (%) / % uptake within 4 weeks of eligibility in 2019 | [-1,Inf] % |

## Consistency and error checking

Data quality has already been checked by PHS.

# Statistical analyses

The following sections are presented separately for each analytical objective. All analyses will be conducted for data from Scotland. Depending on the data available for the other UK nations, similar analyses will be conducted in parallel. At present, the variations in data (in terms of collection methods and availability and varying vaccination policies) suggest that pooling the UK data or conducting a meta-analysis would not be appropriate, however any differing trends may be discussed in a descriptive manner.

## Objective a) Describe the impact of the COVID-19 pandemic on the uptake of immunisations provided at each of the five immunisation contacts offered to pre-school children

### Outcome

The primary outcome is the % uptake of preschool immunisations (represented by uptake of one of the vaccines due at that age) within 4 weeks of eligibility. As a secondary outcome, the % uptake of preschool immunisations by 6 months of age (first dose 6in1) or 16 -18 months of age (first dose MMR) may also be considered to allow for comparisons with data from other nations (TBC).

### Exposures of interest

Time, specifically in time-periods: 2019 (baseline), 01 Jan- 22 Mar 2020 (pre-lockdown), 23 Mar-final week Jul 2020 (lockdown) and Aug-end of Sept 2020 (post lockdown). The start date to 23 Mar has been chosen to correspond with the beginning of the UK wide lockdown as announced by the UK government. The end of the lockdown period is less well-defined and varied both in approach and timescale between Scotland, England, Wales and Northern Ireland. Broadly speaking, by the end of July, there was a substantial reduction in ‘lockdown’ restrictions with the opening of many non-essential businesses and limited indoor meeting between households permitted, therefore a pragmatic approach has been taken to define the lockdown period as 23 Mar 2020 until end Jul 2020. The data included in each time period are shown in Table 4.

Table 4 Definition of time periods

| Time period | Data included |
| --- | --- |
| Baseline 2019 | Aggregate data for whole of 2019 |
| Pre-Lockdown 2020 | Monthly data for Jan 2020 and Feb 2020. Weekly data from W/B 2Mar2020 up to and including W/B 16Mar2020 |
| Lockdown 2020 | Weekly data from W/B 23Mar2020 up to and including W/B 27Jul2020 |
| Post lockdown 2020 | Weekly data from W/B 3Aug2020 up to and including W/B 28Sept2020 |

The primary outcome of interest is comparison between baseline 2019 and lockdown 2020 for each vaccine. Of secondary interest are comparisons between baseline 2019 and pre-lockdown 2020, baseline 2019 and post lockdown 2020, pre-lockdown 2020 and lockdown 2020, lockdown 2020 and post lockdown 2020.

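### Table 4 codes W/B 2, 9 and 16 March 2020 as pre-lockdown although much of each 4-week outcome window falls in lockdown, which biases two secondary contrasts

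*SAP*

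**What the plan says.** Table 2 of the SAP (Data variables available) defines the time variable as "Time-period when preschool child was eligible for immunisation" and the uptake count as "The number of preschool children who received vaccination within 4 weeks of becoming eligible". The Outcome section for Objective a) makes this 4-week uptake the primary outcome.

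Under Exposures of interest for Objective a), the text gives the second period as "01 Jan- 22 Mar 2020 (pre-lockdown"), and Table 4 builds it from "Monthly data for Jan 2020 and Feb 2020. Weekly data from W/B 2Mar2020 up to and including W/B 16Mar2020". Lockdown is "Weekly data from W/B 23Mar2020 up to and including W/B 27Jul2020" and post-lockdown is "Weekly data from W/B 3Aug2020 up to and including W/B 28Sept2020". There is no gap or transition period at either boundary.

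The same section states that "The primary outcome of interest is comparison between baseline 2019 and lockdown 2020 for each vaccine". The other four contrasts, including both that use the pre-lockdown group, are secondary. The Sensitivity analysis entry for Objective a) is empty (None), and the SAP does not discuss windows that cross a boundary.

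**The concern.** A child's period is fixed on the day of eligibility, but the outcome can occur on any of the following 28 days. A child eligible on 22 March is coded pre-lockdown although 27 of the 28 window days come after lockdown began. If lockdown changed uptake in either direction, part of that change is booked to the pre-lockdown group.

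Two secondary contrasts suffer. Pre-lockdown vs lockdown shrinks because the reference group already carries some of the effect. In 2019 vs pre-lockdown, a difference can appear where there was none. That second point matters because 2019 enters only as a whole-year aggregate, so this contrast is the plan's only look at change that preceded lockdown, and an artefact there would read as an earlier trend. The SAP judges significance by whether the 95% confidence interval crosses 1 and analyses the whole eligible population, so a small distortion can look precise.

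**Working it through.** The SAP gives no uptake levels, numbers eligible or timing of vaccination within the window, so there is no stated figure to reproduce. The overlap is calendar arithmetic; the effect on the contrasts needs assumptions, which are marked.

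**Inputs from the SAP.** Window: 28 days. Pre-lockdown: 1 January to 22 March 2020 = 82 days. Lockdown: W/B 23 March to W/B 27 July = 19 weeks = 133 days, ending 2 August. Assumption: the same number of children become eligible each day.

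**Overlap at the start of lockdown** (eligibility day counted as day 1)

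- The first window to reach 23 March belongs to 25 February. From there to 22 March is 27 days: 27/82 = 33%.
- Window-days in lockdown: 1 + 2 + … + 27 = 378, out of 82 × 28 = 2,296, or 16.5%.
- W/B 2 March: 7 to 13 days, mean 10/28 = 36%. W/B 9 March: 14 to 20 days, mean 17/28 = 61%. W/B 16 March: 21 to 27 days, mean 24/28 = 86%.
- January and February alone: (1 + 2 + 3 + 4 + 5)/(60 × 28) = 15/1,680 = 0.9%.
- Counting from the day after eligibility gives 28/82 = 34% and 406/2,296 = 17.7%, so the convention matters little.

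**Overlap at the end of lockdown**

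- Eligibility days 7 July to 2 August reach 3 August or later: 27/133 = 20%.
- Window-days: 378/(133 × 28) = 378/3,724 = 10.2%.

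**If all vaccination falls in the first 2 weeks** (14-day window)

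- Onset: (1 + … + 13)/(82 × 14) = 91/1,148 = 7.9%.
- End: 91/(133 × 14) = 91/1,862 = 4.9%.

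**Share of the true effect kept.** Assumptions: the effect is carried in proportion to window time, there was no true change before lockdown, and uptake returns to the 2019 level from 3 August.

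| Contrast | Even spread over 4 weeks | First 2 weeks only |
| --- | --- | --- |
| Pre-lockdown vs lockdown | 1 − 0.165 − 0.102 = 73% | 1 − 0.079 − 0.049 = 87% |
| 2019 vs pre-lockdown (truth: none) | 16.5% of the effect appears | 7.9% appears |
| 2019 vs lockdown (primary) | 1 − 0.102 = 90% | 1 − 0.049 = 95% |
| Lockdown vs post-lockdown | 90% | 95% |
| 2019 vs post-lockdown | unaffected | unaffected |

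If uptake did not change around 3 August, the end terms vanish. Pre-lockdown vs lockdown then keeps 1 − 0.165 = 84% (even spread) or 1 − 0.079 = 92% (first 2 weeks), and the primary contrast keeps all of its effect.

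A wider range: let each straddling child carry a share s of the next period's effect, with 28 straddling days at each boundary. Pre-lockdown vs lockdown keeps 1 − s(28/82 + 28/133) = 1 − 0.552s, which is 95% at s = 0.1, 72% at s = 0.5 and 45% at s = 1. The primary contrast keeps 1 − 0.211s: 98%, 89% and 79%.

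**Illustration on the odds-ratio scale** (assumed fall from 94% to 88%, even spread)

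- True OR: (88/12)/(94/6) = 0.47.
- Pre-lockdown: 94 − 0.165 × 6 = 93.0%. Lockdown: 88 + 0.102 × 6 = 88.6%.
- Pre-lockdown vs lockdown: −4.4 points, OR 0.58.
- 2019 vs pre-lockdown: −1.0 point, OR 0.85, where the truth is 1.00.
- Primary: OR about 0.50.

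With an assumed fall from 85% to 80% and s = 0.5, the true OR is 0.71; pre-lockdown vs lockdown gives 0.78, the primary 0.73, and 2019 vs pre-lockdown 0.94.

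**Could the artefact look significant?** In the 94% to 88% case, assume 1,000 children eligible per week: 52,000 in 2019 and 82/7 × 1,000 = 11,714 pre-lockdown. The standard error of the log OR is √[1/(52,000 × 0.94 × 0.06) + 1/(11,714 × 0.93 × 0.07)] = 0.041, so z = ln(0.85)/0.041, about 4.0 in size. At 500 per week it is about 2.8. With vaccination only in the first 2 weeks and 1,000 per week it is about 1.9.

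**The case against.** Grouping by eligibility date is a coherent cohort definition. The Population section uses it, the published data are aggregated that way, and reassignment by vaccination date is not possible. The stated aim covers the pandemic as well as its control measures, so a fall among March-eligible children would be a real event under an imprecise label. This explains the choice but does not rescue the label: Table 4 calls the group pre-lockdown, and a reader of Table 5 will take a 2019 vs pre-lockdown difference as preceding lockdown.

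A window that reaches 23 March also does not mean that the child was still unvaccinated then. If most families attend in the first days, the bias is small. This stands, and it is why the size can only be given as a range.

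A reader might infer that all five contrasts are diluted, or that the primary result is compromised. The SAP does not support either reading:

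- The pre-lockdown group does not enter the primary contrast, and children eligible from 23 March have their whole window after lockdown began.
- Only the July weeks touch the primary contrast, and only if uptake changed around 3 August. The SAP itself treats the end of lockdown as a pragmatic choice after gradual easing, so there may be no sharp boundary to misclassify against.
- 2019 vs pre-lockdown is not diluted. If nothing changed before lockdown, the spill moves it away from no effect.
- 2019 vs post-lockdown is untouched.

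**Conclusion.** The concern holds for the two secondary contrasts that use the pre-lockdown group. All three March weeks are coded pre-lockdown with 36%, 61% and 86% of window time in lockdown. The calendar figures assume only a steady daily flow of eligible children.

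The resulting bias is less certain. Pre-lockdown vs lockdown keeps about 73% of the effect under even spread with return to baseline, and about 87% if vaccination is confined to the first 2 weeks. 2019 vs pre-lockdown may show a spurious difference of roughly 8% to 16% of the true effect under the same two timings.

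For the primary contrast the issue is minor and conditional: about 90% of the effect is kept under even spread, and all of it if uptake did not shift around 3 August. The change is recommended; it is not a condition for the primary analysis to stand.

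**What to change.** 1. In Table 4, define pre-lockdown as the January and February 2020 monthly data. Show W/B 2, 9 and 16 March as a transition period that belongs to neither group. Overlap falls from 16.5% to 0.9% of window-days; in the 94% to 88% example the false 2019 vs pre-lockdown difference falls from 1.0 to 0.009 × 6 = 0.05 points. February cannot be trimmed further, because weekly data start on 2 March.
2. Keep the current Table 4 definition of pre-lockdown as a sensitivity analysis.
3. Keep the lockdown period as it stands for the primary, HSCP and SIMD analyses. Prespecify a sensitivity analysis omitting W/B 6 to 27 July for the primary and the lockdown vs post-lockdown contrasts. All windows in the remaining 15 weeks end by 2 August.
4. State in the SAP that periods are assigned by eligibility date and that windows near a boundary straddle it.

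Cost: some SAP wording, a recoded period variable and a few extra model fits. The pre-lockdown group loses three weeks; going from 82 to 60 days raises the standard error of its uptake by about √(82/60) − 1 = 17%. The July sensitivity analysis drops 4 of 19 weeks and raises the lockdown standard error by about √(19/15) − 1 = 13%. That loss from the main exposure group is why the July change belongs in a sensitivity analysis and not in the main definition.
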